# Educational Module Intervention for Radiographers to Reduce Repetition Rate of Routine Digital Chest Radiography in Makkah Region of Saudi Arabia Tertiary Hospitals: Protocol of a Quasi-Experimental Study

**DOI:** 10.2196/resprot.8007

**Published:** 2017-09-26

**Keywords:** repetition rate, intervention, radiographer, quasi-experimental, information motivation behavioral skills model

## Abstract

**Background:**

Repetition of an image is a critical event in any radiology department. When the repetition rate of routine digital chest radiographs is high, radiation exposure of staff and patients is increased. In addition, repetition consumes the equipment’s life span, thus affecting the annual budget of the department.

**Objective:**

The aim of this study is to determine the impact of a printed educational module on reducing the repetition rate of routine digital chest radiography among radiographers in Makkah Region tertiary hospitals.

**Methods:**

A quasi-experimental time series with a control group will be conducted in Makkah Region tertiary hospitals for 8 months starting in the second quarter of 2017. Four hospitals out of 5 in the region will be selected; 2 of them will be selected as the control group and the other 2 as the intervention group. Stratification and a simple random sampling technique will be used to sample 56 radiographers in each group. Pre- and postintervention assessments will be conducted to determine the radiographer knowledge, motivation, and skills and repetition rate of chest radiographs. Radiographs of the chest performed by sampled radiographers in the selected hospitals will be collected for 2 weeks before and after the intervention. A piloted questionnaire will be distributed and collected by a researcher in both groups. One-way multivariate analysis of variance and 2-way repeated multivariate analysis of variance will be used to analyze the data.

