## Methods

### Study Design

The design of this study is basically a quasi-experimental time series with a control group. This design was chosen because the intervention was recommended by other researchers [22,23]. A quasi-experimental study is the only design that could be applied in this study. The difficulty of randomizing by location and subject and the small number of the population make the quasi-experimental design suitable in this study [24]. In addition, there is difficulty in randomizing by subject to avoid potential contamination. Location is also a factor, since no 2 hospitals are similar.

The Makkah Region of Saudi Arabia was selected for the study because the problem has been ignored in the area and the repetition rate has not been periodically measured there [25,26]. Out of 5 hospitals, 4 will be selected to be in the study since randomization is not required in this type of study [27]. The hospitals involved are under the direction of Makkah Region health affairs. Two will be chosen as an intervention group and 2 as a control group. Preintervention assessment will be conducted in both groups at the same time during the second quarter of 2017. The intervention will be distributed to radiographers in the intervention group, and after 1 month, an assessment will be conducted. Six months after the implementation of intervention, a second postintervention assessment will be conducted. Figure 1 demonstrates the study flow.

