### Sample Size

We will use the formula by Lemeshow et al [31] to estimate the minimum sample size required in intervention studies and to test a hypothesis of proportion of 2 population problems in terms of the radiographers sample size (see Figure 2), where *p* 1 and *p* 2 were obtained from a study by Moreira [32] to estimate the sample size of radiographers in each group and Z1–α=1.96, Z1–β=0.842, *p* 1 is 0.63, *p* 2 is 0.88, and *p*^–^=0.755. Figure 3 displays the sample size estimation of the secondary outcome variables.

According to Sullivan [33], the attrition rate (dropout) can be calculated by the formula (desired sample size)/(percent retained). Hence, for this study, a sample size of 56 for each group was targeted.

In terms of the repetition rate of routine digital chest radiographs sample size, the same formula was used, where *p* 1 and *p* 1 were obtained from the study of Zhang and Chu [34] to estimate the sample size of routine digital chest radiography in each group and Z1–α=1.96, Z1–β=0.842, *p* 1 is 0.0584, *p* 2 is 0.087, and *p*^–^=0.0728. Figure 4 displays the sample size estimation of the primary outcome variable.

According to Sullivan [33], the attrition rate that may occur due to any loss of chest images can be calculated by the formula (desired sample size)/(percent retained). The sample size of routine digital chest radiographs is 1618 for each group, and this number is expected to be reached within 2 weeks. Two weeks’ time is similar to that used in the study conducted by Ahmed and Suliman [35].

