### Instruments

A questionnaire developed by the researcher based on the information motivation behavioral skills model is one of the instruments that will be used to evaluate the level of radiographer knowledge about imaging, as well as the motivation and skills. It consists of close-ended questions and is divided into 2 sections: demographic data of the radiographer and domain of the radiographer’s knowledge, motivation, and skills. Radiographers are expected to spend 5 minutes completing the questionnaire.

A check list was recommended and used in several studies around the world to measure the repetition rate of routine digital chest radiographs [8]. It is an international instrument. It contains radiographer demographic data, number of radiographs performed by radiographer, number of repeated radiographs, and causes of repetition. It is completed by the researcher in order to obtain accurate results and overcome biases, using actual numbers. Therefore, its reliability does not need to be checked. Furthermore, studies conducted by Al-Malki et al [12] and Khafaji and Hagi [11] in Saudi Arabia used the same instrument. This means that the check list used in this study is valid.

In order to achieve accurate and precise results, the validity and readability of the questionnaire will be evaluated. Face validity will be ensured by an expert currently practicing to ensure the veracity of the meaning, wording, and sequences. Content validity will be ensured by lecturers working in the university to ensure clarity, representation, and comprehensiveness. Furthermore, factor analysis will be conducted to ensure a structural correlation between variables and factors on the instruments. Finally, reliability through the Cronbach coefficient alpha will be conducted to ensure internal consistency.

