### Statistical Analysis

Data analysis in this study is divided into 2 parts: descriptive and inferential. Descriptive data will be calculated in order to compute the central tendency and dispersion to add valuable statistical information to the study. Inferential data analysis will be used to meet a specific objective. Chi-square, 1-way multivariate analysis of variance, 2-way repeated measure multivariate analysis of variance, and multivariate analysis of covariance are the statistical methods that will be used to test the hypothesis. *Cochran Q test* will be also employed to assess the difference in proportion. The level of significance will be set at α=0.05, and all testing of hypotheses will be conducted using 2-sided tailed hypotheses. The statistical program used is SPSS version 22 (IBM Corp).

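### The named repeated-measures MANOVA is a complete-case method, so a radiographer who misses one of the three assessments drops out along with repetition counts already recorded

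*Protocol article*

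**What the plan says.** The Abstract (Methods) lists knowledge, motivation, skills and the repetition rate as assessed before and after the intervention, and continues: "One-way multivariate analysis of variance and 2-way repeated multivariate analysis of variance will be used to analyze the data." The Statistical Analysis section names both MANOVAs again, adds chi-square, MANCOVA and the Cochran Q test for differences in proportion, and gives SPSS 22 as the software. No test is assigned to an outcome. The Summary in the Discussion describes the study as combining four outcome variables, the repetition rate among them.

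Study Design sets a preintervention assessment, one after 1 month, and a last one: "Six months after the implementation of intervention, a second postintervention assessment will be conducted."

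On loss, Sample Size says that "the attrition rate (dropout) can be calculated by the formula (desired sample size)/(percent retained)", which leads to 56 radiographers per group. The same device, applied to lost images, leads to 1618 radiographs per group. The percentage retained does not appear in the text.

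The two kinds of data come from different sources. Radiographers answer the questionnaire. For the repetition check list, Instruments says: "It is completed by the researcher in order to obtain accurate results and overcome biases, using actual numbers."

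**The concern.** A repeated-measures MANOVA treats each person's outcomes over time as one response vector, and a vector with a gap cannot be used. Attrition is expected and follow-up lasts six months, so some vectors will have gaps. Two losses follow.

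- **Missed assessment.** A radiographer without the 1- or 6-month assessment is dropped, and the valid counts from the other assessments go unused. This happens even if the repetition rate is analysed on its own by this method.
- **Missed questionnaire.** If the repetition rate and the questionnaire scores enter one MANOVA, an unreturned questionnaire also removes primary-outcome data that never depended on the radiographer's response.

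At stake are recorded information on the primary outcome and the comparability of the groups. The Limitations section relies on exact matching to offset the lack of randomisation. Deletion after matching can disturb that balance. Those who stay complete may also differ from those who do not, for instance in how far they took up the printed module.

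**Working it through.** **1. Reproduce the planned numbers.** Inputs from Sample Size: Z = 1.96 and 0.842; p1 = 0.63, p2 = 0.88, mean 0.755 for radiographers; p1 = 0.0584, p2 = 0.087, mean 0.0728 for radiographs. The formula figure is not shown, so I used the usual two-proportion form:

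n = [1.96·√(2p̄(1−p̄)) + 0.842·√(p1(1−p1) + p2(1−p2))]² / (p1−p2)²

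- Radiographers: (1.1921 + 0.4900)² / 0.25² = 2.8297 / 0.0625 = 45.3. Then 45/0.80 = 56.25, so 56.
- Radiographs: (0.7202 + 0.3087)² / 0.0286² ≈ 1294.1. Then 1294.1/0.80 = 1617.7, so 1618.

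Both stated figures fit 80% retention. The 20% loss is therefore back-calculated, not quoted.

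**2. What the inflation covers under a complete-case analysis.** Only radiographers complete at all time points count. Assume baseline is complete and that missingness occurs at the two follow-ups. The patterns below are assumptions; the documents give none. Power is for 0.63 vs 0.88, two-sided 0.05, which is the comparison that sized the radiographer sample for the secondary outcomes.

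| Assumed pattern | Complete per group | Power |
|---|---|---|
| Total loss 20% (same people at both follow-ups) | 56 × 0.80 = 44.8 | about 80% |
| 10% at each follow-up, independent | 56 × 0.90² = 45.4 | about 80% |
| 20% at each follow-up, independent | 56 × 0.80² = 35.8 | about 70% |

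The first two rows leave the planned 45. Only the third falls short.

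**3. What the inflation cannot cover.** Dividing by the proportion retained restores a count. It leaves open whether the retained radiographers resemble those lost, and it does not bring back the deleted counts. In the first row, 56 − 44.8 = 11.2, so about 11 radiographers per group would be deleted although their baseline counts exist.

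**4. Whether the other named tests avoid the problem.** The Cochran Q test also needs complete matched blocks, and it tests change over time, not group by time. Chi-square can take all images but ignores that the same radiographers are measured repeatedly. Neither gives a group-by-time comparison that uses every recorded assessment.

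**The case against.** The strongest reply is that nothing places the repetition rate in the same MANOVA as the questionnaire scores. Chi-square and Cochran Q are also named, and Sample Size treats the primary outcome as a proportion of radiographs with its own allowance for lost images. A reader might infer that a missed questionnaire certainly discards primary-outcome data. The documents do not support that; it holds only if the outcomes are modelled jointly. The loss from a missed assessment remains whenever the named repeated-measures MANOVA is applied.

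A second reply is that missing-data rules belong in an analysis plan that is not shown. That is right, and their absence is not the point here. The point is the named method, which deletes incomplete radiographers by construction, so that a later rule would have to replace it or work around it.

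Third, parts of a possible remedy are already in place. Sampling Methods applies the exclusions to the list before selection, and nothing says that they are reapplied later. The check list is already separate from the questionnaire. Staff on leave or transferred perform no radiographs there, so no model recovers that assessment. All of this stands. What can be kept is their counts from the assessments they did have.

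Fourth, it is tempting to say that deletion filters only the intervention group and so inflates the effect. Questionnaires are collected in both groups and deletion would act in both. Bias in the contrast needs a difference in mechanism between groups, which is plausible but not documented. One can construct a 25% overstatement (1/0.80 = 1.25) by assuming that a deleted fifth of the intervention group had exactly no change. The documents give no basis for that assumption, so the figure should not be used.

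**Conclusion.** The point holds in a limited form. The plan commits to a complete-case method for data from three assessments, with attrition expected. It would discard recorded repetition counts for radiographers who miss an assessment and, if the outcomes are modelled jointly, for those who miss only a questionnaire. Completer bias is possible in either group and could disturb the exact matching. Its direction and size cannot be derived from the documents.

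A reader might conclude that the study is underpowered. That is not shown. If the implied 20% is total loss, about 45 radiographers per group remain and power is about 80%, as planned. The figure of 36 per group with about 70% power needs an assumed independent 20% missing at each follow-up. It also concerns the secondary-outcome calculation, not the power for the repetition rate.

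**What to change.** - Analyse the repetition rate in its own group-by-time model: a binomial mixed model (or GEE) for the number of repeats out of radiographs performed, per radiographer and assessment. Use every recorded assessment, whether or not questionnaires were returned.
- Analyse knowledge, motivation and skills with a mixed model on all available data.
- Report missing assessments by group.

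The cost is a change of analysis wording, with no added participants or assessments. The downside is an assumption to state: the mixed model relies on data being missing at random, and a standard GEE on missing completely at random.

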### Outcome Measure

#### Primary Outcome

The primary outcome of this research is the repetition rate of routine digital chest radiographs. It is the change of the behavior based on the information motivation behavioral skills model.

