## Discussion

### Summary

This quasi-experimental time series with control group aims to investigate the effect of printed educational material on radiographer knowledge, motivation, and skills and the radiography repetition rate.

Educating radiographers helps reduce the dose of radiation exposure on patients, decreases waiting time, and increases patient satisfaction. A reduction in the repetition rate decreases the dose of radiation and reduces the workload. This intervention is significant to the organization as it reduces the burden of equipment consumption and cost as well as assists the organization in achieving its vision and goals. In addition, implementing an educational program that focuses on reducing the repetition rate of radiographs has been highly recommended [12,40,41].

To our knowledge, this is the first study that combines 4 outcome variables—knowledge, motivation, skills, and the repetition rate of routine digital chest radiography—and aims to investigate the effect of using printed educational material on the repetition rate of routine digital chest radiography. Furthermore and based on our knowledge, this is the first study that analyzes the repetition rate among radiographers.

The intervention module will be made available in both English and Arabic languages, and participants can choose their preferred language to complete the sessions. The intervention program was designed to be as brief as possible to increase readability. The printed educational material was selected because of the difficulty of assembling radiographers from different cities in one place at one time. There is a need to overcome the issue of bias to increase the credibility of the study. The quasi-experimental design is one of the strongest designs for this particular research.

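### No listed test is tied to the primary repetition rate, and neither MANOVA, chi-square nor Cochran Q suits a controlled before-after comparison of it

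*Protocol article*

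**What the plan says.** Under Primary Outcome the article states: "The primary outcome of this research is the repetition rate of routine digital chest radiographs". Knowledge, motivation and skills are secondary.

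Sample Size treats the primary outcome on its own, as two proportions of radiographs, with "Z1–α=1.96, Z1–β=0.842, *p* 1 is 0.0584, *p* 2 is 0.087". It concludes: "The sample size of routine digital chest radiographs is 1618 for each group". Radiographers are sized separately: "Hence, for this study, a sample size of 56 for each group was targeted".

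The Methods part of the abstract lists all four outcomes as assessed before and after the intervention and then says: "One-way multivariate analysis of variance and 2-way repeated multivariate analysis of variance will be used to analyze the data". The Statistical Analysis section repeats these two methods, adds MANCOVA and chi-square, and mentions Cochran Q for a difference in proportion. It also sets the error rate ("The level of significance will be set at α=0.05", and "all testing of hypotheses will be conducted using 2-sided tailed hypotheses"). It does not say which method tests repetition, nor which variables enter the MANOVA. The Discussion summary says "this is the first study that combines 4 outcome variables".

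Study Design gives two hospitals per group and three assessments: baseline, 1 month and 6 months.

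**The concern.** The study question is whether repetition changed more in the intervention hospitals than in the control hospitals. That is a group-by-time contrast on one outcome, a count of repeats out of images taken. The sizing follows this logic for a single proportion. The analysis list does not. Its only method that addresses group by time is a repeated MANOVA, built for several continuous outcomes.

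Two things are at stake. First, repetition may be tested by a method that does not fit the data or answers a different question. Second, if the four outcomes share one MANOVA, its null hypothesis is that none of them changed. A printed module that only raises questionnaire scores could then give P<.05 with repetition unmoved.

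**Working it through.** **1. The plan's own figure.** Inputs from Sample Size: z = 1.96 and 0.842, p1 = 0.0584, p2 = 0.087, mean 0.0728. The usual two-proportion formula is

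n = [1.96·√(2·0.0728·0.9272) + 0.842·√(0.0584·0.9416 + 0.087·0.913)]² / 0.0286² ≈ 1294.

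The retained percentage is not in the text. Assuming 80%, 1294.1/0.8 = 1617.7, so 1618, the stated figure. The sizing therefore assumes a separate test of repetition.

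**2. Each listed method against the question.**

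| Method | Compares groups | Uses baseline | Fit to repeats out of images |
|---|---|---|---|
| Cochran Q | No | Within one set of units only | Needs the same units at each time; the images differ between periods |
| Chi-square on pooled images | Yes, at one time | No | Ignores clustering by radiographer |
| Repeated MANOVA | Yes | Yes | Assumes normal responses with equal variance; complete cases only |

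One-way MANOVA does not use baseline. MANCOVA could take baseline as a covariate, but makes the same distributional assumptions.

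**3. How far the rates are from normal.** If the minimum 1618 images are spread over 56 radiographers, each has 1618/56 ≈ 28.9 images. Expected repeats are 28.9 × 0.0584 ≈ 1.7 and 28.9 × 0.087 ≈ 2.5. The share with no repeats is 0.9416^29 ≈ 17% and 0.913^29 ≈ 7%. If twice as many images were collected, expected repeats would be about 3.4 and 5.0, and the shares with none about 3% and 0.5%. Denominators will differ with workload in either case.

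**4. Complete cases.** With three assessments, each complete independently in an assumed 90% to 95% of radiographers, 56 × 0.90³ ≈ 41 to 56 × 0.95³ ≈ 48 remain. At the 80% retention assumed above, the number planned to remain is 56 × 0.8 ≈ 45. So the count may or may not fall short; the firm point is that partial data are discarded.

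**5. Specificity, if all four outcomes share one MANOVA.** I use the two-group Hotelling T² with 4 outcomes, 56 per group and α = 0.05. The noncentrality is (56/2)·δ′R⁻¹δ, and the test is F on 4 and 107 degrees of freedom. R has one common correlation, with outcomes coded so that higher is better. Effects and correlations are assumptions.

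Rejection rate with no repetition effect:

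| Assumed shift | r = 0 | r = 0.3 | r = 0.5 |
|---|---|---|---|
| 0.3 SD in all three questionnaire outcomes | 56% | 43% | 45% |
| 0.5 SD in all three | 96% | 89% | 91% |
| 0.8 SD in knowledge alone | 93% | 97% | 99% |

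**6. Power for repetition.** Take a repetition effect of 0.534 SD, which gives 80% power in a single-outcome test with 56 per group.

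| Four-outcome test | r = 0 | r = 0.3 | r = 0.5 | r = 0.7 |
|---|---|---|---|---|
| Only repetition moves | 58% | 67% | 81% | 96% |
| All four move by 0.534 SD | 99.8% | 91% | 81% | 71% |

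Power can be lost or gained, depending on the correlations and on which outcomes move.

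**The case against.** The strongest reply is that the article keeps repetition apart. It is the sole primary outcome, has its own sample size, and its expected P<.05 is stated separately in the abstract's Results. Statistical Analysis also lists chi-square and Cochran Q, which plausibly serve a proportion. A reader might infer from the abstract that repetition is tested only within a four-outcome MANOVA. The text does not support that: other tests are listed, and the MANOVA's dependent variables are never given. The remark about combining four outcome variables is a claim of novelty, not an analysis rule. Nor does any sentence say that success would be declared on an omnibus result.

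A reader might also infer that MANOVA dilutes a real repetition effect. That holds at low correlation when only repetition moves. It vanishes near a correlation of 0.5 and reverses above it. The article itself expects the constructs to be correlated and all four outcomes to improve, so a general loss of power cannot be claimed.

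Finally, lists of dependent variables and follow-up tests are often left to a fuller document. That is fair, and their absence is not the point here. The point is that the methods the article does name do not suit its primary comparison, and the reply leaves that standing.

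**Conclusion.** The point holds in this form: the primary repetition rate has no test assigned to it, and none of the methods named suits a controlled before-after comparison of repeats out of images. The analysis list also does not match a sizing based on one pair of proportions.

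The misfit of MANOVA is clear at the planned minimum of about 29 images per radiographer, and weaker if many more images are collected. Non-specificity is conditional on the MANOVA covering all four outcomes. In that case, a significant result with no repetition effect would occur in about 89% to 96% of studies for 0.5 SD shifts in the other three, and in about 43% to 56% for 0.3 SD shifts, at correlations of 0 to 0.5. The SD effects, correlations, 80% retention and per-assessment completeness are assumptions, not figures from the article.

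**What to change.** Make the primary analysis one binomial mixed model of repeats out of images. Include hospital fixed effects, period and group-by-period terms, a radiographer random intercept, and all available assessments. Leave out a separate group main effect. Each hospital belongs to one group, so hospital absorbs it: with four hospitals and three periods, the full set of terms has 9 columns but rank 8. The group-by-period terms remain estimable.

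State which follow-up, 1 month or 6 months, carries the primary group-by-period contrast. Analyze knowledge, motivation and skills separately as secondary outcomes; MANOVA may be kept for these.

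The cost is analysis wording and work, with no extra data collection, and SPSS 22 can fit generalized linear mixed models. The downside is that there is no single joint test of the four outcomes. The model also cannot separate the intervention from changes over time peculiar to a hospital, a limit of having two hospitals per group that the listed methods share.
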